### Intervention

#### Preoperative administration of CNs

Following enrollment, surgery should be performed within 2 weeks (including day 14). In addition to routine preoperative management, peritumoral submucosal CNs injection is administered 1 day before surgery in CNs group and dual tracer group. Carbon nanoparticles suspension injection (Chongqing Lummy Pharmaceutical Co., Ltd.) is diluted into 25 mg/ml with saline and then injected using “sandwich method.” Briefly, approximately 0.5 ml saline is firstly injected into the submucosal layer for mucosal elevation. Then, 0.2 ml CNs is injected. Finally, 0.5 ml saline is injected again to prevent leakage of CNs. This injection is performed at both proximal and distal sides of tumor under gastroscopy.

#### Intraoperative lymph node localization and dissection

After anesthesia, ICG (Dandong Yichuang Pharmaceutical Co., Ltd.) powder is diluted into 2.5 mg/ml with saline and then injected into subserosal layer using “hexa-site” method in the ICG group and dual tracer group [18]. Briefly, the injection is performed at 3 sites along the lesser curvature (first branch of left gastric artery, angular and first branch of right gastric artery). Similar injection was repeated along the greater curvature.

A near-infrared (NIR) fluorescence imaging system (PINPOINT, NOVADAQ, Mississauga, ON, Canada) is used to obtain near-infrared fluorescence imaging during surgery. It provides high-definition white light visual field, near-infrared fluorescence visual field, and ICG-specific SPY visual field as well as merged visual field. LN dissection in the ICG group and dual tracer group is performed under the fluorescent laparoscope.

The standard sequence of LN dissection is as follows: (1) total gastrectomy: No. 6 → No. 7, 9, 11p → No. 8a, 12a, 5 → No.1 → No. 4sb → No. 4sa, 11d → No.2; (2) distal subtotal gastrectomy: No. 6 → No. 7, 9, 11p → No. 3, 1 → No. 8a, 12a, 5 → No. 4sb. Selective dissection of No.10 LNs is performed when (1) the primary tumor is located in the middle/upper stomach and invaded a large extent, (2) preoperative radiology suggests splenic lymphadenopathy, (3) significant fluorescent signal of No. 10 LNs, and (4) black stained No. 10 LNs by CNs. Surgical area is routinely inspected for possible residual fluorescent LNs or black-stained LNs, and additional dissection will be performed if necessary. D2 + LN dissection will be performed if fluorescent or black-stained LNs (such as No. 10 or No. 14v) are observed outside D2 region.

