### Outcome

The primary outcome is the total number of retrieved LNs. The secondary outcomes include positive rate, false positive rate, negative rate, false negative rate, number of metastatic LNs, rate of LN metastasis, relationship between LN metastasis and dual staining, morbidity and mortality, 3-year disease-free survival rate, 3-year overall survival rate, 3-year recurrence rate, postoperative recovery, duration of surgery, changes in body weight, intraoperative blood loss, intraoperative mortality, incision length, body temperature, and changes in lab parameters (albumin, prealbumin, hemoglobin, white blood cells, C-reactive protein, etc.).

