## Discussion

Gastric cancer is one of the most common malignancies worldwide, especially in Asia. It has been widely accepted that extensive lymphadenectomy is associated with improve prognosis of patients with gastric cancer. In recent years, navigation surgery using ICG or CNs has been increasingly applied in laparoscopic gastrectomy. Nonetheless, single tracer technique demonstrates certain drawbacks in clinical practice. This study proposes a new strategy using dual tracers (ICG with CNs) for LN visualization in laparoscopic gastrectomy, which is expected to raise the number of retrieved LNs and eventually improve the prognosis of patients.

Dual tracer navigation for lymph node dissection in laparoscopic radical gastrectomy can potentially bring several benefits. Compared with ICG alone, (1) it may reduce false negative rate, which is the most significant limitation of current ICG application; (2) it can optimize the tumor localization; and (3) it can decrease the possibility of surgical field contamination during the leakage of ICG. Compared with CNs alone, (1) lymphatic blockage by tumor cells can affect the distribution of CNs in metastatic LNs. At this point, ICG with smaller molecular weight is able to show lymphatic networks that hardly be reached by CNs, and (2) the combination of the two tracers is beneficial to detect lymph nodes in abnormal anatomical locations and improve lymph node detection rates, leading to accurate pathological staging and treatment plan. All above advantages eventually result in better prognosis of patients with gastric cancer.

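### Dissection outside D2 is partly triggered by staining, so false negative and false positive rates taken over all retrieved nodes suffer partial verification

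*Protocol article*

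**What the plan says.** Under Intraoperative lymph node localization and dissection, the protocol article gives three routes by which staining can lead to removal of tissue.

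- **Beyond D2:** "D2 + LN dissection will be performed if fluorescent or black-stained LNs (such as No. 10 or No. 14v) are observed outside D2 region".
- **No. 10:** four conditions are listed. Two do not involve staining: "Selective dissection of No.10 LNs is performed when (1) the primary tumor is located in the middle/upper stomach and invaded a large extent" and "2) preoperative radiology suggests splenic lymphadenopathy". Two do: "3) significant fluorescent signal of No. 10 LNs, and (4) black stained No. 10 LNs by CNs".
- **Final sweep:** "Surgical area is routinely inspected for possible residual fluorescent LNs or black-stained LNs, and additional dissection will be performed if necessary".

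For No. 14v, staining is the only trigger stated. The Outcome section lists "positive rate, false positive rate, negative rate, false negative rate" among the secondary outcomes and names no set of nodes for them. The Data analysis section mentions positive rates together with the number of retrieved nodes, which suggests a denominator of all retrieved nodes but does not fix it. In the Discussion, the first advantage claimed for the dual tracer over ICG alone is that "it may reduce false negative rate, which is the most significant limitation of current ICG application".

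**The concern.** These rates set stain status against pathology, and a node left in the patient has no pathology. Inside the standard field, stations come out whatever their stain. Outside it, some stations come out because something in them stained. An unstained metastatic node in such a station, left in place because nothing there stained, can never be counted as a false negative. An unstained benign node there can never be counted as a true negative. The test under evaluation thus helps to decide which nodes are checked against the reference standard.

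At stake are the tracer-accuracy outcomes, and above all the false negative rate, which carries the leading argument for the dual tracer over ICG. The ICG, carbon-nanoparticle (CNs) and dual arms have different stain triggers, so a comparison between them uses differently selected sets of nodes. The primary outcome, the total node count, is a separate matter.

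**Working it through.** **The plan's own figure.** The article states no false negative or false positive rate. Its only computed figure is the sample size. That reproduces (one-sided t-test power 0.802 at 103 per group; 103/0.8 = 128.75, so 129; 4 × 129 = 516) and is not an input here.

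**Direction.** Let P and N be the metastatic and non-metastatic nodes in all stations considered. Let FN and FP be the unstained metastatic and stained non-metastatic nodes. Let M and T be the metastatic and non-metastatic nodes left in place because nothing in their station stained. All of these are unstained, so:

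- False negative rate (FNR): FN/P under full verification, (FN − M)/(P − M) as observed. The shortfall is M × (1 − FN/P)/(P − M), never negative.
- False positive rate (FPR): FP/N under full verification, FP/(N − T) as observed. The excess is (FP/N) × T/(N − T), never negative.

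**Size, on assumed inputs.** The article gives none, so all of the following are assumptions.

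- 35 D2 nodes, 12% metastatic; 4 nodes outside D2, 6% metastatic.
- Probability of staining, metastatic/non-metastatic: ICG 0.6/0.5, CNs 0.5/0.4.
- Probability that the tracer reaches the outside station: ICG 0.6, CNs 0.3.
- The tracers act independently; a dual stain means either one.
- A triggered station is removed whole, and there is no trigger other than staining.

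ICG arm, step by step:

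- P = 4.2 + 0.24 = 4.44; N = 30.8 + 3.76 = 34.56.
- FN = 4.44 − (4.2 × 0.6 + 0.24 × 0.6 × 0.6) = 1.8336; full FNR = 0.413.
- FP = 30.8 × 0.5 + 3.76 × 0.6 × 0.5 = 16.528; full FPR = 0.478.
- Chance that a node in a reached station is unstained: 0.06 × 0.4 + 0.94 × 0.5 = 0.494; for the other three nodes together, 0.494³ = 0.1206.
- M = 0.4 × 0.24 + 0.6 × 0.24 × 0.4 × 0.1206 = 0.103; T = 0.4 × 3.76 + 0.6 × 3.76 × 0.5 × 0.1206 = 1.640.
- Observed FNR = (1.834 − 0.103)/(4.44 − 0.103) = 0.399; observed FPR = 16.528/(34.56 − 1.640) = 0.502.

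The same steps for each arm:

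| Arm | M | T | FNR full → observed | FPR full → observed | D2-only FNR, FPR |
|---|---|---|---|---|---|
| ICG | 0.103 | 1.640 | 0.413 → 0.399 | 0.478 → 0.502 | 0.400, 0.500 |
| CNs | 0.176 | 2.774 | 0.519 → 0.499 | 0.370 → 0.402 | 0.500, 0.400 |
| Dual | 0.075 | 1.210 | 0.219 → 0.205 | 0.666 → 0.690 | 0.200, 0.700 |

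If 30% of outside stations are dissected for reasons other than staining, M and T fall by 30% and the shifts shrink by about as much. The observed FNR is then 0.403, 0.505 and 0.209, and the observed FPR 0.495, 0.392 and 0.682.

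**Range.** The inputs were varied over 15,552 combinations: 25 or 40 D2 nodes; 2, 4 or 6 outside; metastatic share 10% or 20% inside and 3% or 10% outside; metastatic staining 0.4 to 0.8 for ICG and 0.3 to 0.7 for CNs; non-metastatic staining 0.3 or 0.5 and 0.2 or 0.4; reach 0.3 to 0.9 and 0.1 to 0.6; other triggers 0 or 30%. The direction never reversed. Results for ICG, CNs and dual:

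- FNR too low by medians of 0.8, 1.2 and 0.8 points (overall range 0.05 to 12.3).
- FPR too high by medians of 1.5, 1.9 and 1.7 points (overall range 0.3 to 9.8).

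**Which arm.** The dual arm had the largest absolute FNR bias in 13% of combinations and the largest absolute FPR bias in 34%. In relative terms it was largest in 71% for FNR and in none for FPR.

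**The case against.** The strongest reply is that the article never prescribes the pooled analysis. It names the rates without a node set, and their operational definition may stand in a fuller document that is not shown. That is fair, and it is why the point is conditional on a denominator of all retrieved nodes. The retrieval rule itself is stated, however, and it creates the problem for that denominator.

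A reader might infer three stronger claims that the documents do not support.

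- *Stations outside D2 reach pathology only when stained.* No. 10 also has triggers based on tumour site and extent and on radiology. The final sweep concerns the surgical area, which need not lie outside D2.
- *The bias is worst in the dual arm and favours it.* Two dyes trigger more stations and so leave fewer unexamined. In the worked example the ICG-minus-dual FNR contrast is 19.4 points both fully verified and as observed. The CNs-minus-dual contrast moves from 30.0 to 29.4 points, against the dual arm.
- *A spurious dual advantage can be quantified.* Suppose that stain-selected metastatic nodes amount to 5% of in-field metastatic nodes with ICG and 10% with dual. A common in-field FNR of 30% then appears as 0.30/1.05 = 28.6% and 0.30/1.10 = 27.3%. At 40% it appears as 38.1% and 36.4%. The gap of 1.3 to 1.7 points comes entirely from the assumed 5% and 10%. The Introduction's own remark that CNs accumulate less in distant nodes does not encourage that doubling.

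It is also true that restricting to the standard field does not recover the missed false negatives. In the example the dual D2-only rates (0.200 and 0.700) lie further from full verification (0.219 and 0.666) than the observed ones (0.205 and 0.690). Across the combinations, the observed dual FNR was below the D2-only value in only 9%, and the observed FPR above it in 16%. The restriction changes what is estimated. Its merit is that the rates then rest on a field verified irrespective of stain in every arm.

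**Conclusion.** The concern holds in limited form. Rates taken over all retrieved nodes have a false negative rate that is too low and a false positive rate that is too high, compared with full verification of the same stations. That direction needs no assumption beyond some stations being left in place because nothing in them stained. The size rests wholly on assumed staining, reach and node counts. One to a few points is plausible, and other triggers for No. 10 reduce it. The verified node set differs between tracer arms, but the documents do not allow the bias to be ranked by arm, and no net advantage to the dual arm can be inferred. Only the secondary accuracy outcomes are affected; the sample size is not. The change is worth making because it is cheap and the false negative rate carries a main claim of the trial.

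**What to change.** - **Analysis sentence:** for the between-arm comparison, compute the staining-accuracy rates only on nodes from stations dissected irrespective of staining in the procedure performed. No. 10 counts only where tumour location or radiology triggered its dissection. State that the rates apply to that field.
- **Separate table:** report nodes from stain-triggered dissection (No. 10, No. 14v, other tissue beyond D2) and from the final sweep by arm, outside these rates.
- **CRF:** record the station of each node group and the trigger for any dissection beyond the standard field. The surgical and pathology items listed in the article name neither.
- **Wording:** reconcile the No. 10 list with the sentence on dissection beyond D2. The list is joined by a conjunction that, read literally, requires both dyes, which no single-tracer or control patient could meet. The other sentence accepts either stain.

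The cost is one sentence and two data items. A few nodes per arm leave the denominator, and the rates say nothing about stations outside the stated field. Surgery does not change.

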### Data collection

Data will be collected and entered into the database by clinical investigators and supporting trial personnel on both electronic and paper-based case report forms (CRFs). Specific contents are as follows:

#### Intraoperative data collection

##### Video data

Intraoperative LN dissection and postoperative specimen profile will be photographed and archived for each participant. Furthermore, the entire laparoscopic procedure will be videotaped, and the unclipped files will be saved for evaluation. All photos and videos will be stored in hard drivers for a minimum of 3 years. The procedure will be judged as disqualified if photographs or videos are incomplete.

##### Surgical parameters

The following information will be recorded: (1) name of leading surgeon; (2) procedure duration; (3) procedure type especially digestive tract reconstruction method; (4) incision length; (5) whether converted to open surgery and reason; (6) intraoperative blood loss; (7) blood transfusion volume; (8) tumor location; (9) maximum diameter of tumor size; (10) whether distant metastasis is observed and, if any, the location of metastasis; (11) proximal and distal resection margin, radical cure (R0/R1/R2); (12) intraoperative complications including vascular injury, organ injury, tumor rupture, hypercapnia, emphysema, subcutaneous emphysema, air embolism, allergic reactions, etc.; (13) intraoperative death if occurs.

#### Postoperative parameters

The following information will be recorded: (1) pathological findings including histological type, distant metastasis and location, NIH risk grade, and degree of radical surgery (R0/R1/R2); (2) postoperative complications of which the severity is graded according to the Clavien-Dindo system and serious complication is defined as grade III or above; (3) lab parameters including blood routine test (hemoglobin, red blood cells count, white blood cells count, lymphocyte count, neutrophil count and percentage, platelets count, monocyte count, etc.) and blood biochemistry (albumin, prealbumin, total bilirubin, indirect bilirubin, direct bilirubin, AST, ALT, creatinine, urea nitrogen, total cholesterol, triglyceride, fasting blood glucose, potassium, sodium, chloride and calcium, etc.); (4) postoperative recovery including time to first ambulation, time to first ventilation, time to liquid diet, postoperative highest body temperature, time to gastric tube withdrawal, daily gastric juice drainage volume, time to abdominal drainage tube withdrawal, daily abdominal drainage tube drainage volume, blood transfusion volume from the surgery to discharge, and postoperative hospital stay.

#### Follow-up records

Before discharge, various forms of health education such as dietary brochure and popular science lecture are provided to each participant to clarify the importance of regular follow-up visits. For patient who fails to visit on time for reexamination, telephone contact will be carried out to advise prompt reexamination. All participants will be followed-up every 3 months for the first 2 years and every 6 months since the third year (i.e., 1, 3, 6, 9, 12, 15, 18, 21, 24, 30, and 36 months) after discharge. Table 1 will be filled out at each visit. Tumor recurrence or metastasis and survival status of all participants will be assessed accordingly.

**Table 1 Tab1:** Follow-up sheet for each participant

Time point since surgery (month)	1	3	6	9	12	15	18	21	24	30	36
Actual date	√	√	√	√	√	√	√	√	√	√	√
Physical examination	√	√	√	√	√	√	√	√	√	√	√
Blood routine	√	√	√	√	√	√	√	√	√	√	√
Blood biochemistry	√	√	√	√	√	√	√	√	√	√	√
Tumor related indicators	√	√	√	√	√	√	√	√	√	√	√
Chest plain scan	√	√	√	√	√	√	√	√	√	√	√
Upper gastrointestinal endoscopy					√				√		√
Abdominal CT			√		√		√		√	√	√
Abdominal ultrasound	√	√				√		√			

### Date management

Electronic CRFs will be stored in a standardized database with periodical backups, and paper CRFs will be submitted to the trial office. Prior to enrollment, clinical investigators and statistical analysts will receive uniform training in data entry, date extraction, and data analysis. The study database will be exposed only to trial staffs who have been trained and authorized. Data analysts will extract data from CRFs and review data for accuracy and completeness. For participants with missing data, missing values will not be supplemented, and the participants will be withdrawn from the study.

Identity and privacy of the participants will be strictly protected. Each enrolled participant will be assigned a subject ID number after signing the informed consent form. This unique ID number will represent the subject’s identity and be entered into the database. Data collected from subject will be stored under the ID number. Several measures will be taken to minimize the disclosure of subjects’ personal information, including (1) only authorized investigators can link the trial data chain of subjects to the subjects themselves through the identification form maintained by the study site, and (2) regulators and supervision departments of this study will conduct on-site review on the original data and strictly keep confidential. Data collection, transfer, processing, and storage will comply with data protection and privacy regulations throughout the study.

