### Sample size

This study is a superiority testing trial (one-tailed trial) of which the primary outcome is the number of retrieved LNs and study subjects will be divided into 4 groups. Combined with our previous findings and literature reports, the standard deviation σ of the total number of LNs in control group was 8.6 [9, 13, 17]. The *α* (test level) is set as 0.05 and power (1-β) is 0.8. A difference of more than 3 in the total number of detected LNs will be considered as significant, i.e., the effect value *d* = 3/*σ* = 0.35. Thus, at least 103 (102.3) participants are required in each group. Considering an expected dropout rate of 20%, 129 (128.75) participants are finally required in each group, leading to a total of 516 participants.

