### Data analysis

Database will be established using Epidata 3.0, and statistical analysis will be performed using SPSS 18.0. This trial uses differential testing; a *p*-value less than 0.05 will be considered statistically significant, and the confidence intervals for the parameters will be estimated as 95%.

In this trial, validity analysis based on MITT (modified intention to treat) analysis will be conducted. The primary and secondary outcomes will be analyzed with both MITT and PP (per protocol) analysis. Conclusion of MITT analysis will be the primary analytical method, and if the conclusions of PP analysis and MITT analysis are consistent, the credibility of the conclusions can be improved. SP (safety population) analysis will be used to analyze laboratory evaluations, adverse events, and adverse reaction data. SP will be defined as the denominator for the incidence of adverse reactions.

Descriptive statistics will be used to systematically describe primary and secondary outcomes. Means, standard deviations, and confidence intervals will be presented based on data from the control group and intervention groups. Frequency distributions, percentages, medians, and mean rank order will be presented based on quantitative data and rank data. Positive rates, positive number, and total number of retrieved LNs will be presented based on qualitative data. The number of events, number of missingness, median survival time, and survival rate will be presented based on survival data. Efficacy analysis will be performed on data following descriptive statistics. This study utilizes Pearson chi-square test for qualitative data, *t* test for quantitative data, Wilcoxon rank sum test for ranked data, Log-rank test for univariate analysis and Cox regression model for multivariate analysis of survival data, and two-tailed test for safety indicators and incidence of adverse reactions.

Abnormal values will be judged when the observed value is greater than P75 or less than P25, and 3 times more than the interquartile range defined as P75 subtracts P25. Sensitivity analysis will be performed on the abnormal data, and the data will be retained if results are not contradictory. If there is a contradiction, specific analysis will be conducted.

Subgroup analysis will be performed to identify risk factors for the prognosis according to the specific circumstances of the data.

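### The missing-data rule withdraws the participant instead of limiting the loss to the affected analysis, so read literally it discards observed lymph-node counts and is not reconciled with the MITT and survival analyses.

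*Protocol article*

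**What the plan says.** The rule is in the Date management section of the protocol article. Where a participant has missing data, "missing values will not be supplemented, and the participants will be withdrawn from the study". It is stated once, and nothing elsewhere narrows it. Missing data is not among the eight items under Withdrawal criteria.

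Three other parts of the article bear on it:

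- **Outcome:** "The primary outcome is the total number of retrieved LNs". This is known once the surgical specimen has been examined.
- **Follow-up records:** 11 visits from month 1 to month 36, with 79 ticked entries per participant in Table 1. Patients who miss a visit are telephoned.
- **Data analysis:** MITT is the primary analysis and PP is supportive. Survival data are analysed by log-rank test and Cox regression, and "The number of events, number of missingness, median survival time, and survival rate will be presented based on survival data". The word censoring does not appear.

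**The concern.** Declining to impute is a defensible choice. The problem is the second half of the sentence, which attaches the consequence to the participant and not to the missing value or to the analysis that needs it.

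For the primary outcome, an observed lymph-node count could be lost because of a blood test or visit missed months or years later. The set compared would then be selected by what happened after randomisation, in a trial where neither surgeons nor participants are blinded. That sits badly with an MITT primary analysis.

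For DFS and OS, log-rank and Cox methods use a patient's follow-up up to last contact and then censor. Removing the patient discards that information. The removal also depends on outcome: a patient who dies early has few visits to miss, whereas a survivor must complete all 11. Withdrawal may also end data collection, in which case later survival status could not be recovered at analysis.

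**Working it through.** **1. The plan's own sample size.** Inputs from the Sample size section: "This study is a superiority testing trial (one-tailed trial"; α "is set as 0.05 and power (1-β) is 0.8"; the standard deviation "of the total number of LNs in control group was 8.6"; difference 3 nodes; dropout 20%.

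- Effect size: 3/8.6 = 0.349.
- One-sided two-sample t-test, α 0.05, power 0.80: n = 102.3, rounded up to 103 per arm.
- Dropout: 103/0.8 = 128.75, rounded up to 129. Total 4 × 129 = 516.

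The stated figures reproduce, so the defect lies in the missing-data rule and not in the arithmetic.

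**2. Effect of the literal rule on numbers and power.** The article gives no missingness rate. Assume that each visit is incomplete with probability q, independently over the 11 visits. The fraction of patients due all 11 visits who are complete is (1 − q)^11. Power is one-sided at 5%, difference 3, SD 8.6, from the noncentral t distribution.

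| Assumed q | (1 − q)^11 | Remaining of 129 | Power |
|---|---|---|---|
| 0% | 1 | 129 | 87% |
| 1% | 0.895 | 115.5 | 84% |
| 2% | 0.801 | 103.3 | 80% |
| 3% | 0.715 | 92.3 | 76% |
| 5% | 0.569 | 73.4 | 68% |

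The 20% allowance is used up when (1 − q)^11 = 0.8, that is q = 1 − 0.8^(1/11) = 2.0% per visit, before any loss under the listed withdrawal criteria. Patients who die early have fewer visits to miss, so true attrition would be somewhat smaller than the table shows.

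**3. Effect on 3-year mortality if incomplete patients are removed.** Assume true mortality of 25%, with deaths spread evenly so that a patient who dies was due k = 1 to 10 visits. Deaths are retained with probability m, the mean of (1 − q)^k over k = 1 to 10. Survivors are retained with probability s = (1 − q)^11. Apparent mortality is 0.25m / (0.25m + 0.75s).

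- q = 3%: m = 0.849, s = 0.715; 0.2122/(0.2122 + 0.5365) = 28.3%.
- q = 5%: m = 0.762, s = 0.569; 0.1906/(0.1906 + 0.4266) = 30.9%.

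Adding deaths before the first visit (k = 0) gives 28.7% and 31.5%, so that simplification matters little.

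**4. A second illustration, with loss to follow-up in place of missed visits.** Assume exponential event and loss times and non-informative loss of 10% or 20% over 36 months. Deleting lost patients instead of censoring them moves a true 3-year survival of 70% to 68.8% or 67.3%. Over true survival of 60% to 80%, the shift is about 1 to 3 points.

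**The case against.** The strongest reply is that the sentence belongs to data management and speaks of withdrawal from the study, not exclusion from every analysis. The Data analysis section governs who is analysed. It names MITT, log-rank and Cox, and its count of missingness beside the count of events may well mean censored cases. On that reading follow-up stops but earlier data are kept.

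This stands in part. A reader might infer that the plan has replaced censoring with deletion. The article does not say so, and its choice of survival methods points the other way. What can be said is that the two sections are not reconciled. The milder reading is possible but is written nowhere, and an analyst following the sentence as it stands would drop the patient.

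A reader might also infer that the primary analysis has become a 36-month complete-case analysis. The article does not say when the lymph-node count will be analysed, so that is only one literal consequence.

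Nor does Follow-up records contradict the rule. Its statement that "Tumor recurrence or metastasis and survival status of all participants will be assessed accordingly" describes scheduled assessment and defines no analysis set. The telephone contact also means that a missed date need not become missing data.

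On size, the rates are assumptions and nothing in the article anchors them. Missed visits tend to cluster within patients, so fewer patients would be affected at the same average rate than independence implies. At 2%, power equals the planned 80%. Loss unrelated to arm and to node count costs precision only.

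**Conclusion.** The concern holds as a badly fixed rule and an unresolved inconsistency. It is not a detail left to the analysis plan, because the article itself states the rule, without limit. Read literally, it removes observed lymph-node counts from the primary comparison and removes incompletely followed patients from DFS and OS, and it makes inclusion depend on events after randomisation.

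The size is illustrative. Under independent incompleteness of 2% to 5% per visit, 103 down to 73 of 129 per arm remain and power falls to between 80% and 68%, against about 87% with all counts kept. At 3% to 5%, a true 3-year mortality of 25% would appear as about 28% to 31%. That is a distortion of level. No difference between arms has been computed, and bias in the comparison would require loss related to arm together with outcome or prognosis. The defect in the wording does not depend on these rates.

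**What to change.** Delete the clause that withdraws participants with missing data, and state instead:

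- Every observed lymph-node count of a patient in the MITT set enters the primary analysis, whatever is missing later.
- For DFS and OS, follow-up continues despite missing items, and patients in the analysis set are censored at last known status.
- A missing secondary value excludes the patient from that analysis only.
- A sensitivity analysis addresses missing lymph-node counts.

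The change should stay within missing data. Requiring all randomised patients in every analysis would override the stated MITT set and the listed withdrawal criteria, which are separate questions.

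The cost is a wording amendment, best made while follow-up data can still be collected. Denominators will differ between outcomes and must be reported for each.
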